### Sample size

Based on previous literature, we estimate an effect size of 0.25. The G*Power V.3.1.9.7 software^48^ was employed to determine the requisite sample size. Assuming that the probability of error does not exceed α=0.05 and that the power (1−β) is at least 0.95, an analysis of variance with three groups and two time points with N=66 subjects can demonstrate an effect size of 0.25. Based on previous research projects, we calculate a drop-out rate of 20%, which increases the total sample size to N=82.

### Risk to patients

Possible risks that can arise, particularly during the VR intervention, are cybersickness^49^ and increased stress levels or anxiety due to the complex technical setup and instructions. In addition, the sensory isolation from the environment can lead to a feeling of loss of control. To counteract this, it was ensured that at least one person from the study team was always present with the patients during the intervention. Patients were able to contact the study team directly if they had any questions, problems or felt unwell. In addition, care was taken to ensure that patients were shielded from disturbances as much as possible. During the data collection phase, study personnel will be present to monitor and record any spontaneously occurring adverse events; if such events occur, they will be discussed with the treating physician and reviewed during the weekly team meetings. Patients will continue to receive ongoing medical care after the end of the trial, where potential side effects can still be discussed. In addition, short-term access to psycho-oncological support will be provided through the department of psychosomatic medicine and psychotherapy for patients who express a need for psychological support after study completion.

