### Primary outcome measure

#### State-Trait Anxiety Inventory (STAI-state)

The STAI^36^ is a self-report questionnaire that can assess both situational state-anxiety and stable trait-anxiety. The short version with 10 items was used to assess the situational state-anxiety as the primary outcome.^36^ The response for each of the 10 items is based on an 8-point Likert scale (1=‘not at all’; 8=‘completely’). Four items need to be inverted before calculating the total score. The STAI-state score ranges between 10 and 80. Higher values indicate higher state-anxiety. The STAI reveals excellent internal consistency of α=0.90.^36^

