#### Fear of Progression Questionnaire Short Form

The Fear of Progression Questionnaire Short Form (PA-F-KF)^42^ consists of 12 items that are answered on a 5-point Likert scale (1=‘never’; 5=‘very often’). The questionnaire assesses the patient’s fear of progression on five dimensions (affective reaction, partnership/family, occupation, loss of autonomy) and shows overall good internal consistency (α=0.87).^42^ The construct validity of the items was confirmed by correlating the items to other measures assessing similar constructs (Hospital Anxiety and Depression Scale, HADS; Posttraumatic Stress Disorder Checklist - Civilian Version, PCL-C; Short Form-8 Health Survey, SF-8; Life Attitude Profile – Revised, LAP-R). A factor analysis revealed a one-dimensional structure, explaining 42% of the total variance.^42^ The psychometric properties were also confirmed in more recent studies. For example, a study by Hahn^43^ found an internal consistency of α=0.88 for the PA-F-KF.

#### Minimal Documentation System version 2

The Minimal Documentation System (MIDOS-2)^44^ is a self-report questionnaire assessing participants’ symptom-related afflictions due to chemotherapy-associated side effects on a 4-point Likert scale (0=‘none’; 3=‘major afflictions’). In total, there are 13 items. Ten items are measuring the side effects pain, nausea, regurgitation, shortness of breath, constipation, weakness, lack of appetite, fatigue, depression and anxiety. Two more items leave open spaces for naming other afflictions and one more item assesses how the participant is feeling that day, ranging from 0 (‘very bad’) to 4 (‘very good’). The sum score of each item describes the extent of complaints for each participant. The questionnaire reveals good psychometric properties, with internal consistencies varying between α=0.67 and 0.73 and the test-retest variability varying between r=0.69 and r=0.57.^44^ The psychometric properties were also confirmed for patient groups in non-palliative care.^45^

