### Data monitoring and management

A randomisation file will be used to allocate a participant code to the intervention arms. A recruitment file is used to allocate the participant code to all included patients and, further, contains patients’ diagnoses, medical clearance and information about the recruitment process (treating physicians’ approval for study participation, checklist for how many attempts were needed to meet the patient in the IAC, date of informed consent). A data file contains pseudonymised survey data of patients for each measurement time point. Another file will be used to anonymously assess drop-outs, screening failures and reasons for non-participation or lack of interest. The data will be entered by the study team accountable for implementation of the study and will be double-checked by another team member. Supervision by the study team during chemotherapy sessions ensures the questionnaires are fully completed by participants. Data records will be kept separate from the consent forms. Data records of patients who did not meet the inclusion criteria (screening failures) will be disposed of in accordance with data protection regulations. After collection, salivary cortisol samples will be temporarily stored in a freezer (−20°C) and sent to a laboratory (Dresden LabService GmbH, Technical University of Dresden, Germany). Questionnaires and cortisol levels derived from saliva samples will be stored as combined research data for at least 10 years (in accordance with the principles of Good Clinical Practice). Access to the anonymised final trial dataset will be granted on request to the study team; the intended use of the data must be disclosed, after which the appropriate dataset will be provided.

Patients will receive standard medical care during the whole participation. No adverse side effects are expected due to the interventions and participating patients do not face higher risks compared with patients who are not participating in the current study. As a member of the study team will supervise each session, participants can terminate the intervention at any time. Participants can report any side effects to the study team and use the evaluation questionnaires for thorough feedback. Therefore, study monitoring is not needed.

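### Cybersickness and loss of control are named as VR risks, but no prompted item for either is described and another section says no side effects are expected; VR-specific harms may be under-counted and not comparable between arms.

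*Protocol article*

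**What the plan says.** The Risk to patients section opens: "Possible risks that can arise, particularly during the VR intervention, are cybersickness". It adds "increased stress levels or anxiety due to the complex technical setup and instructions" and a feeling of losing control caused by isolation from the surroundings. For recording harms it says that "study personnel will be present to monitor and record any spontaneously occurring adverse events". Such events are then discussed with the treating physician and reviewed in weekly team meetings.

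The Data monitoring and management section says: "No adverse side effects are expected due to the interventions and participating patients do not face higher risks". It also cites standard medical care, a supervisor at each session and freedom to stop, and adds: "Participants can report any side effects to the study team and use the evaluation questionnaires for thorough feedback". It concludes: "Therefore, study monitoring is not needed".

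On what patients are asked, the STAI-state section says: "The short version with 10 items was used to assess the situational state-anxiety as the primary outcome". The MIDOS-2 section says: "Ten items are measuring the side effects pain, nausea, regurgitation, shortness of breath, constipation, weakness, lack of appetite, fatigue, depression and anxiety". It also describes two open items for other complaints and one on general wellbeing that day. Table 2 places STAI-state, VAS-anxiety and MIDOS-2 before and after the intervention, with no restriction by arm, and the Measures section repeats them at T1 and T2.

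The feasibility paragraph of the Statistical analysis section lists side effects among its sources. The Randomisation section says the study team is not blinded after enrolment.

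**The concern.** Two things do not fit together. First, one section lists harms that the headset exercise might cause, while another treats the interventions as free of expected side effects and of added risk. The eligibility criteria agree with the first: they exclude epilepsy, claustrophobia and conditions affecting balance or visual perception.

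Second, the harms most specific to VR are the ones that no described questionnaire item asks about. A count built from what staff happen to notice or patients happen to mention depends on how attentive the staff are and how forthcoming the patients are, and both may differ by arm when everyone knows who wears the headset. Feasibility is a stated aim, and side effects feed that judgement. A low VR count could mean that the exercise is well tolerated or that the symptoms were not asked about, and the trial could not tell which.

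**Working it through.** The plan gives no figure for harms, so the check is mainly a comparison of passages.

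**Step 1: risk statements.** Risk to patients: three possible harms, chiefly of VR. Data monitoring and management: no side effects expected and no higher risk than for non-participants. Both cannot stand as written.

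**Step 2: each named harm against the described measures.**

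| Named harm | Asked in all arms, before and after, T1 and T2 | Not asked by a fixed item |
|---|---|---|
| Raised stress or anxiety | STAI-state, VAS-anxiety, VAS-relaxation, MIDOS-2 anxiety item | – |
| Cybersickness | MIDOS-2 nausea and regurgitation; two open MIDOS-2 items | Dizziness, disorientation, eye strain |
| Loss of control | Two open MIDOS-2 items only | Loss of control |

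**Step 3: the other routes.** The items described for the evaluation questionnaire cover usability, liking, relaxation, boredom and annoyance, with free-text fields. The form is tailored by arm and given once, after T2, so a patient who leaves after T1 because of VR symptoms may never complete it. Patients with less than 10 minutes of intervention in a session are classed as dropouts. Reasons for dropout are recorded, but the article describes the dropout file as anonymous and does not say whether reasons can be linked to arm.

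**Step 4: illustration of what incomplete capture could do.** The planned total of 82 gives 82/3 = 27.3, so about 27 VR patients. Let p be the true proportion with symptoms and c the share recorded. Neither is in the documents; both are assumptions. The expected number recorded is 27·p·c, and the chance of recording at least one case is 1 − (1 − p·c)^27.

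| p | c | Expected recorded | Chance of at least one |
|---|---|---|---|
| 10% | 100% | 2.7 | 0.94 |
| 10% | 50% | 1.35 | 0.75 |
| 10% | 25% | 0.68 | 0.50 |
| 20% | 100% | 5.4 | 0.998 |
| 20% | 50% | 2.7 | 0.94 |
| 20% | 25% | 1.35 | 0.75 |

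An expected count of 2.7 arises both from a 10% rate fully recorded and from a 20% rate half recorded. Without a common question, c is unknown and may differ by arm, so the count does not identify the rate.

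**The case against.** A reader might infer that harms are recorded only when they surface by themselves, or that no question is common to the arms. The documents do not support this. Raised anxiety is the primary outcome and is measured before and after every session in every arm. MIDOS-2 asks about nausea and invites every patient to name other complaints. Heart rate and blood pressure are taken every 5 minutes, and a structured form records disruptions. A staff member is present throughout, so recording does not depend on patients volunteering symptoms.

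A reader might also infer that monitoring is waived solely because no side effects are expected. The section gives several other grounds, and these remain whatever becomes of that premise.

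A third tempting reading is that VR harms will be under-counted. That is a plausible risk for cybersickness and loss of control, but it is not shown, and it has no support for anxiety. The evaluation form (appendix D) and the session documentation form are not shown, so a relevant prompt in either cannot be excluded. Item-level tables by arm are commonly left to an analysis plan, so their absence is no fault.

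All of this stands and narrows the point. It does not remove the contradiction between the two sections. Nor does an open item replace a fixed one: it depends on the patient thinking to mention the symptom, and MIDOS-2 is framed around complaints from chemotherapy. An item in appendix D would still come only after T2.

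**Conclusion.** The point holds in a limited form. The two sections contradict each other on expected harms and must be reconciled. For dizziness, disorientation, eye strain and loss of control, no prompted item is described, so recording rests mainly on spontaneous events noted by unblinded staff, supplemented by the open MIDOS-2 items. Counts may be too low and may not be comparable between arms, which weakens one stated basis of the feasibility judgement. The primary anxiety analysis is not affected.

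The size cannot be derived from the documents. With about 27 VR patients and assumed true rates of 10% to 20%, recording a quarter to a half of cases gives 0.68 to 2.7 expected cases, against 2.7 to 5.4 with full recording. These figures show only how much depends on the unknown share recorded. The conclusion also assumes that the forms not shown contain no such prompt after each session.

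**What to change.** 1. Add the same few yes/no items (dizziness or disorientation, eye strain, headache, loss of control) to the postintervention questionnaire in all three arms at T1 and T2, and report counts by arm. If collection is under way, do this for the remaining patients and state how many were asked. If a form not shown already asks this in all arms after each session, say so in the article instead.
2. From data already collected, report by arm how many patients score higher after than before on STAI-state and on the MIDOS-2 nausea item, and list the open MIDOS-2 entries.
3. Reword the Data monitoring and management section so that it agrees with the risks named under Risk to patients, and state which grounds for the monitoring decision remain.

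The cost is a short form amendment, probably with ethics notification, and a few extra tables; no extra staff are needed. Prompted items will also pick up chemotherapy symptoms, for which the control arm gives the comparison. If the form can no longer be changed, the second and third steps need no new data.

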### Data monitoring and management

A randomisation file will be used to allocate a participant code to the intervention arms. A recruitment file is used to allocate the participant code to all included patients and, further, contains patients’ diagnoses, medical clearance and information about the recruitment process (treating physicians’ approval for study participation, checklist for how many attempts were needed to meet the patient in the IAC, date of informed consent). A data file contains pseudonymised survey data of patients for each measurement time point. Another file will be used to anonymously assess drop-outs, screening failures and reasons for non-participation or lack of interest. The data will be entered by the study team accountable for implementation of the study and will be double-checked by another team member. Supervision by the study team during chemotherapy sessions ensures the questionnaires are fully completed by participants. Data records will be kept separate from the consent forms. Data records of patients who did not meet the inclusion criteria (screening failures) will be disposed of in accordance with data protection regulations. After collection, salivary cortisol samples will be temporarily stored in a freezer (−20°C) and sent to a laboratory (Dresden LabService GmbH, Technical University of Dresden, Germany). Questionnaires and cortisol levels derived from saliva samples will be stored as combined research data for at least 10 years (in accordance with the principles of Good Clinical Practice). Access to the anonymised final trial dataset will be granted on request to the study team; the intended use of the data must be disclosed, after which the appropriate dataset will be provided.

Patients will receive standard medical care during the whole participation. No adverse side effects are expected due to the interventions and participating patients do not face higher risks compared with patients who are not participating in the current study. As a member of the study team will supervise each session, participants can terminate the intervention at any time. Participants can report any side effects to the study team and use the evaluation questionnaires for thorough feedback. Therefore, study monitoring is not needed.

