#### Implementation and quality assurance of the intervention

To optimise intervention effectiveness, several strategies are being implemented. Recruitment data, reasons for non-participation (via a screening questionnaire) and dropout rates are systematically documented to assess feasibility. Following recruitment, participants receive standardised instructions for correct VR and music intervention application. Additionally, study staff are trained to provide consistent guidance and address technical difficulties.

To further ensure procedural consistency, a structured documentation form includes a checklist for standardisation and records start/end times and disruptions. Noise-cancelling headphones are used to minimise external distractions, ensuring participants can fully engage in the intervention.

Furthermore, weekly team meetings facilitate continuous process evaluation, allowing for structured feedback on data collection, recruitment challenges and potential implementation barriers. At the end of the study, feasibility and user experience data, including responses from an evaluation questionnaire, will be analysed to identify challenges and potential areas for improvement.

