### Statistical analysis

All characteristics collected in the study are described in detail using descriptive methods. Qualitative characteristics are indicated by absolute and relative frequencies. Quantitative characteristics are described using mean values, SD, median, minimum and maximum. Parametric analysis methods are used to evaluate the primary and secondary target variables. If assumptions for parametric tests are violated, appropriate non-parametric alternatives will be considered.

Situational anxiety as the primary outcome (measured using the STAI-state) is analysed using separate 3×2 mixed factorial analyses of variance (ANOVAs) for each of the two chemotherapy sessions, with the between-subject factor ‘intervention’ (VR vs music vs control) and the within-subject factors ‘time’ (before vs after intervention). A probability of error of α=0.05 is set. The unit of analysis is individual patients. Effect sizes will be reported using partial eta squared (η²) for ANOVA analyses. Cohen’s d is calculated for post-hoc comparisons when appropriate. The secondary outcome criteria are analysed exploratively, also using ANOVAs and post hoc tests as appropriate. There is no adjustment of the probability of error. The statistical analysis is carried out with the help of standard statistical software (SPSS V.29). Participants will be included in the statistical analysis if they have completed both assessment time points and received the intervention for a minimum of 10 min per session. Furthermore, the intervention must be administered in consecutive sessions as scheduled. Participants who do not meet these criteria will be classified as dropouts. Both an intention-to-treat analysis and a per-protocol analysis will be performed. The results will be compared and discussed.

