The feasibility of the intervention will be evaluated based on multiple data sources. A descriptive analysis of the screening and recruitment data will provide insights into patient participation and reasons for non-participation. Additionally, feasibility will be assessed based on study staff documentation during data collection sessions, as well as recorded reasons for dropout, and potential side effects. Furthermore, the evaluation questionnaire, which includes both usability assessment and self-developed items, will be analysed. The participants’ comments in the free text fields of the evaluation questionnaire will be categorised based on their content into issues and suggestions for improvement.

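### Drop-outs are to be logged anonymously, so a randomised patient's reason for stopping cannot be linked to that patient's record and its link to arm is not assured

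*Protocol article*

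**What the plan says.** The Data monitoring and management section of the protocol article describes several files. On allocation it says: "A randomisation file will be used to allocate a participant code to the intervention arms". The recruitment file also uses that code. On outcomes: "A data file contains pseudonymised survey data of patients for each measurement time point". On people who leave or never join: "Another file will be used to anonymously assess drop-outs, screening failures and reasons for non-participation or lack of interest".

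The Statistical analysis section defines a drop-out as a patient who misses an assessment time point, receives less than 10 minutes of intervention in a session, or does not have the sessions consecutively as scheduled: "Participants who do not meet these criteria will be classified as dropouts". It then promises: "Both an intention-to-treat analysis and a per-protocol analysis will be performed", with the two sets of results to be compared and discussed. Its feasibility paragraph relies on staff session documentation "as well as recorded reasons for dropout, and potential side effects", and on the evaluation questionnaire.

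The section on implementation and quality assurance adds that "dropout rates are systematically documented to assess feasibility", and that "a structured documentation form includes a checklist for standardisation and records start/end times and disruptions".

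**The concern.** Anonymity suits people who declined or failed screening. Randomised patients are different: they have a code, an arm, baseline scores and often T1 scores, and the value of a stated reason for stopping lies in reading it next to these.

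Two parts of the plan depend on that. The Introduction sets out to identify what influences the feasibility of VR and of music, which calls for reasons by arm. The Risk to patients section names problems expected mainly with VR (cybersickness, stress from the technical setup, a feeling of lost control). The Sample section lists causes of termination that could occur in any arm, such as physical weakness or disease progression. Telling these apart needs reason and arm together. In addition, if the intention-to-treat and per-protocol results differ, the first question is why patients left the per-protocol set.

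This is a rule about how data are collected. A link that was never recorded cannot be restored by a later analysis plan.

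**Working it through.** The point concerns data linkage, so the main check sets the sources side by side. The arithmetic only shows how many patients are involved.

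**1. What each source can supply for a randomised drop-out**

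| Source | Linked to the patient? | Shows | Reason for stopping? |
|---|---|---|---|
| Randomisation file | Yes, by code | Arm | Not stated |
| Data file | Yes, pseudonymised | Which time points are missing; baseline and earlier scores | Not stated |
| Session documentation form | Not stated | Start and end times, disruptions | Not stated; a session that never took place may have no form |
| Evaluation questionnaire | Formats tailored to arm | Usability, liking, comments | Given only after T2, so it misses earlier leavers |
| Drop-out file | No, described as anonymous | Drop-outs, screening failures, non-participation | The only file said to cover drop-outs; arm neither stated nor excluded |

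The first two rows give drop-out number and timing by arm, and a comparison of drop-outs with completers on baseline measures and, for those who reached T1, on T1 STAI-state. By Table 2, STAI-state is first taken before the intervention at a session, so a patient who leaves before T1 has only baseline measures. No linked source is said to hold the reason.

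**2. The plan's own figures (Sample size section)**

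Inputs: effect size 0.25 (taken as Cohen's f), alpha 0.05, power 0.95, three groups, two time points, N = 66, drop-out 20%, total 82. A correlation of 0.5 between time points is my assumption; the article does not give one.

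- Noncentrality = f² × N × m / (1 − ρ) = 0.0625 × 66 × 2 / 0.5 = 16.5. On 2 and 63 degrees of freedom the power is 0.953, so N = 66 is reproduced for the group-by-time interaction.
- 66 / 0.80 = 82.5, against the stated 82: agreement to within rounding. No figure in the plan is disputed here.

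**3. How many patients the point touches**

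- Expected drop-outs: 0.20 × 82 = 16.4, about 16.
- Patients per arm: 82 / 3 = 27.3, about 27.
- Drop-outs per arm if spread evenly: 16.4 / 3 = 5.5, so 5 or 6.

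**4. Illustration of what is lost if the log omits arm**

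Suppose, hypothetically, that 8 of 16 entries give discomfort as the reason. The coded files would still show how many left each arm, and that limits the ambiguity.

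- Even drop-out, VR losing 6: the other arms lose 10 and could hold all 8 entries, so the VR count runs from 0 to 6, which is 0% to 6/27 = 22% of the arm.
- Even drop-out, VR losing 5: the VR count runs from 0 to 5, which is 0% to 5/27 = 19%.
- If drop-out were uneven and all 8 were VR patients, the figure would be 8/27 = 30%. An even spread of the 8 would give (8/3)/27 = 10% per arm.

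The figure of 8 has no source in the article. It shows only how wide the uncertainty about VR tolerability could be.

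**The case against.** The strongest reply is that an anonymous log need not omit arm or session, and the article does not say that it does. That stands: the loss of the link to arm is a risk and not an established fact. But with only 5 or 6 drop-outs expected per arm, a log holding arm and session could often be matched to the missing records in the coded file, and would then hardly be anonymous. The description needs correcting either way.

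A second reply is grammatical. The sentence may attach reasons only to non-participation and lack of interest, so that reasons for drop-out are kept elsewhere. That is possible, but the article names no other place for them.

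Third, log fields are a detail that a condensed article may leave to the full protocol. Silence on fields would indeed be no finding. Here, however, the article states a rule, and taken as written that rule works against its own feasibility aim.

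Fourth, some reasons reveal the arm by themselves. A complaint about the headset must come from a VR patient, because the other groups try VR only outside data collection. That stands, but does not help with unspecific reasons such as discomfort, distress or too much effort.

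A reader might infer more: that feasibility by arm and the missing-data assumptions cannot be examined at all. The documents do not support this. The coded files allow the usual check of whether drop-out depends on arm, baseline or T1 scores, and session documentation and the arm-specific evaluation also inform feasibility. Recorded reasons would help to judge a missing-data assumption but would not settle it.

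**Conclusion.** The point holds in a limited form. Taken as written, the protocol separates a randomised patient's reason for stopping from that patient's scores and session record, and does not assure that the reason can be read by arm. The expected number affected is about 16 of 82, assuming the planned 20% drop-out. Counts, timing and observed predictors of drop-out by arm are unaffected, as are the sample size and the primary analysis.

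The consequence is a weaker feasibility assessment of VR and music, and a thinner basis for explaining any difference between the intention-to-treat and per-protocol results. The conclusion rests on reading the anonymous file as carrying no participant code, which fits the contrast with pseudonymised data in the same section, and on no other coded source holding the reasons. It is worth changing because the change is small, but it does not invalidate the trial.

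**What to change.** For every patient who drops out after randomisation, record the reason under the participant code, with arm, session and minutes of intervention received, and report reasons by arm. Restrict the anonymous file to non-participants and screening failures.

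The Ethics and dissemination section lets patients withdraw without explanation and have stored personal data deleted on demand. The coded entry therefore needs a category for no reason given, and must be covered by the deletion procedure. The same section says that personal identifiers will be pseudonymised, which fits coded entry. The consent form is not at hand, so its coverage should be confirmed.

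If reasons have already been logged without a code, say so as a limitation and report them for all arms together, alongside drop-out counts and timing by arm from the coded files.

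The cost is minor extra data entry in files that already exist.
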